### Participants and Procedure

The study population consists of patients aged 18 years or older with a primary alcohol problem, who are currently following TAU at Tactus Addiction Treatment Institute in the Netherlands. One general inclusion criterion is accessibility and ability to use the Internet, since patients will need to access CBM-training online. Two exclusion criteria apply for the TAU: (1) serious psychiatric illness with a risk to decompensate while decreasing alcohol consumption; and (2) the possibility of severe physical illness as a consequence of decreased alcohol consumption. There are no additional criteria for participation in this study.

Patients for the training are recruited by therapists at Tactus Addiction Treatment Institute. After the regular intake procedure, including baseline questionnaires, the TAU starts. Before the patient reaches the goal-setting assignment, the therapist will inform the patient about the CBM training and provide the patient with further information about the study. If the patient wants to participate, an informed consent form will be provided to patients by the therapist. After signing the form, the patient receives login credentials for the CBM training from the researcher.

After finishing registration, the patient is randomly assigned to the Alcohol Avoidance Training or to the placebo training, and receives an email with a link to the CBM training website. After logging in, the patient receives instructions about the training. At the start of each session, the patient is asked to complete the additional questionnaires for the purpose of this study, consisting of self-reported weekly alcohol consumption and desire for drinking. Each of the eight training session takes about 10-15 min. The first training session is preceded by an (online) preassessment and the final training session is followed by an (online) postassessment. Three and six months after the postassessment, each patient will receive online follow-up questionnaires. In case of nonresponse, the patient will be reminded by email or phone to complete the questionnaire.

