### Randomization

Patients will be automatically assigned to one of the two conditions (Alcohol Avoidance Training or placebo training, as described in the Intervention section) with an equal likelihood, using the method of minimization [51] in order to balance for type of TAU (online vs face-to-face). The randomization will be computer-generated without any involvement by the investigators. Patients will be randomly allocated to the condition to which the fewest participants of that type of treatment have so far been assigned.

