### Blinding

The trial has a double-blind design because neither patients nor therapists know to which condition patients are assigned. To ensure anonymity, patients receive an email with a user ID to create their personal research account. If necessary, patients can contact the researcher for help. Patients complete the training at their own computer. To keep patients blind to their intervention condition, patients respond to an irrelevant feature (orientation of the picture) instead of the content of the picture (alcoholic beverage vs soft drink beverage) [23]. During the postassessments, patients’ awareness of the experimental condition is assessed by means of a manipulation check.

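### Read as written, the allocation rule forces every second patient within a TAU type, although the protocol calls it random

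*Protocol article*

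**What the plan says.** Under Randomization, the protocol article says that patients are assigned to the two conditions "with an equal likelihood, using the method of minimization", with TAU type (online or face-to-face) as the only balancing factor. It then gives the rule: patients are "randomly allocated to the condition to which the fewest participants of that type of treatment have so far been assigned". It states no assignment probability for the case where the arms differ, and no rule for ties. It adds: "The randomization will be computer-generated without any involvement by the investigators".

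Under Blinding it says that "neither patients nor therapists know to which condition patients are assigned". The researcher is not named as blinded. Under Participants and Procedure, "Patients for the training are recruited by therapists at Tactus Addiction Treatment Institute", and allocation follows consent and registration.

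The Statistical Analyses section specifies a logistic regression for the primary outcome. Baseline confounders enter only where that is judged necessary, and TAU type is not named as a covariate.

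**The concern.** A rule that sends each patient to the smaller arm leaves nothing to chance once the arms differ. The sentence therefore calls an allocation random when the rule has already fixed it.

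An unpredictable sequence keeps knowledge of one patient's arm from revealing the next patient's arm. Here, anyone who learned the arm of the latest patient in a TAU type, and knew that the arms had been level before that patient, would know the next allocation in that type for certain. The therapists who treat current patients also invite new ones, so predictability would be unwelcome if arms ever became known.

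The wording also matters for reporting. A reader of the results should be able to tell whether the trial used minimization with a random element or, in effect, blocks of two.

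**Working it through.** **Inputs from the protocol.** Two conditions; one factor with two levels; the rule quoted above (Randomization); 152 patients per condition, so 304 in total (Sample Size Calculation).

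**The plan's own figure.** The protocol gives no figure for predictability. The sample size used here does reproduce: for 68% against 81%, one-sided alpha 0.05, the exact power of Fisher's test is 0.7999 at 151 and 0.8030 at 152 per condition. The allocation point does not affect it.

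**Assumptions.** Ties are split 1:1. The protocol does not say so, and this is the most favourable case; a fixed tie rule would make every allocation determined. The online share is not given, so 50%, 70% and 90% were tried.

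**Step 1: the rule as written.** Let D be the absolute difference between the arms within one TAU type.
- D = 0: a 1:1 draw, after which D = 1.
- D = 1: the smaller arm is fixed, after which D = 0.

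Patients 1, 3, 5, ... of a type are ties and patients 2, 4, 6, ... are forced. This is permuted blocks of two within TAU type.

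**Step 2: share forced.** With n1 and n2 patients in the two types, the forced count is floor(n1/2) + floor(n2/2). For a total of 304 this is 152 if both are even and 151 if both are odd: 152/304 = 50.0% or 151/304 = 49.7%. Simulation (500 runs at each online share) gave 49.8% at all three shares.

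**Step 3: correct guesses with the history known.** Half of the allocations are certain and half are coin tosses: 0.5 × 1 + 0.5 × 0.5 = 0.75. Simulation gave 0.749.

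**Step 4: marginal probability.** The first patient of a pair has probability 0.5 of either arm, and the second gets the opposite arm, so also 0.5. Simulation over the first ten positions gave 0.498 to 0.502. Given the history, the probability at every second patient is 0 or 1.

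**Step 5: a biased coin.** Assign the smaller arm with probability p and the larger with q = 1 − p, with 1:1 at ties.
- Long-run share of ties: π0 = 1 / (1 + 1/(p − q)).
- Correct guesses: 0.5 × π0 + p × (1 − π0).
- Mean imbalance per type: (π0/p) / (1 − q/p)².

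| p | Share of ties | Forced | Correct guesses |
|---|---|---|---|
| 1 (as written) | 0.500 | about 50% | 0.75 |
| 0.8 | 1/(1 + 1/0.6) = 0.375 | 0% | 0.1875 + 0.5 = 0.6875 |
| 0.7 | 1/(1 + 1/0.4) = 0.286 | 0% | 0.143 + 0.5 = 0.643 |

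At p = 0.8 the mean imbalance per type is (0.375/0.8) / (0.75)² = 0.46875/0.5625 = 0.83 patients. Simulation at 0.8 gave 0.686 correct guesses. The largest overall imbalance in 500 runs was 6 patients, against 2 under the rule as written.

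**The case against.** The strongest reply is that a journal article compresses the algorithm into one sentence and cites a method paper. The program may contain a random element that the sentence omits. That stands, and it is why the first step is to check the program. It does not save the sentence: if a random element exists, the sentence misdescribes it.

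The second reply is that the risk is remote. Allocation is automatic and follows consent. All eligible TAU patients are to be invited, with no extra criteria for the study, so there is little formal room for selective enrolment. Patients respond to picture tilt rather than content, the mapping of tilt to response is counterbalanced, and awareness of condition is measured at postassessment. The 75% figure requires the past allocations in a type, or at least the arm of the immediately preceding patient of that type. Nothing indicates that a therapist sees the enrolment order across all recruiting therapists. This also stands and keeps the practical weight low.

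Third, the gain from a biased coin is modest, from 75% to about 69% correct guesses, and no effect on bias, type I error or power has been shown. That is fair. The clearer gain is that no allocation remains certain.

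A reader might also infer that the claim of equal likelihood is false. The documents do not support that: with 1:1 ties, each arm has probability one half at every position. The claim fails only conditionally on the history, about which the protocol asserts nothing.

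**Conclusion.** The point holds as a flaw in the stated rule. Read literally, with ties split 1:1, the scheme is blocks of two within TAU type, with about 50% of allocations forced and about 75% guessable from the history. Describing the patient as randomly allocated is wrong at every second patient of a type. The pattern runs within each TAU type, not along the overall enrolment sequence, where the types interleave.

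A reader might conclude that concealment failed or that therapists could steer enrolment. The documents do not support this: no route to the allocation history is described, and several safeguards are. The active training does show alcohol pictures only in the avoid format, so a patient could notice, but that a patient would notice and pass it on is conjecture.

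The importance is minor and the correction is cheap. The sample size is unaffected.

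**What to change.** 1. Check the allocation program for the probability given to the under-represented arm and for the tie rule.
2. If there is no random element, assign the under-represented arm with a probability below 1 (for example 0.8) and draw 1:1 at ties for the remaining patients. Record the date of the change, and report earlier allocations as blocks of two within TAU type.
3. If there already is a random element, leave the program alone and correct the sentence under Randomization to state the probability and the tie rule.
4. Include TAU type as a prespecified covariate in the primary logistic regression, so that the analysis follows the factor used in allocation. This is an addition to the current plan. It does not conflict with the decision not to differentiate between TAU subgroups, because adjustment is not a subgroup analysis.

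**Cost.** One parameter in the program, a protocol note, and one extra term in the model. The article describes recruitment as still open, so a change for the remaining patients is possible. The downside is a chance imbalance of typically about one patient per TAU type, occasionally a few more.

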### Blinding

The trial has a double-blind design because neither patients nor therapists know to which condition patients are assigned. To ensure anonymity, patients receive an email with a user ID to create their personal research account. If necessary, patients can contact the researcher for help. Patients complete the training at their own computer. To keep patients blind to their intervention condition, patients respond to an irrelevant feature (orientation of the picture) instead of the content of the picture (alcoholic beverage vs soft drink beverage) [23]. During the postassessments, patients’ awareness of the experimental condition is assessed by means of a manipulation check.

### Sample Size Calculation

An a priori statistical power analysis (G-power) was conducted to determine the necessary number of participants. The primary outcome measure is a reduction in alcohol consumption. To obtain an estimate of the effect size to be expected, studies describing previous Alcohol Avoidance Training interventions were inspected [21,23]. In both these studies, a relative increase of 20% was observed in effectiveness of TAU + CBM as compared to TAU. The proportion of patients reaching long-term abstinence increased by 13% from 41%-54% [23]. Although in these studies a different dependent measure was used (prolonged abstinence from alcohol), we assume a similar increase in success rate of +13 percentage points as effect size. It has been shown that the Web-based treatment resulted in a 68% success rate (ie, reaching the low-risk drinking criterion) [52]. When extrapolating that to this study, a +13 percentage points additional effect of the Alcohol Avoidance Training is predicted to result in 81% achieving the safe drinking criterion (beta>.80; alpha (one-tailed) <.05). Based on these parameters, 152 patients are needed within a condition to show the hypothesized effects using a Fisher’s exact test for proportions in two independent samples.

### Statistical Analyses

Analyses will be conducted in agreement with intention-to-treat principle. Missing data points will be handled using multiple imputation [53]. One-way ANOVAs and χ²-tests will be performed to see if there are any significant differences at baseline between the two CBM training conditions (Avoid Alcohol vs placebo) for any of the demographic variables or outcome measures. Nonsignificant differences will indicate successful randomization. To determine the primary outcome, a logistic regression analysis will be used to test the differences in the proportion of patients reaching the low-risk drinking criterion between the CBM Alcohol Avoidance Training and CBM placebo condition, both at posttest and at follow-up. If necessary, baseline confounders will be controlled for, and significant interaction effects will be further investigated using post hoc *t*-tests (independent samples *t*-test and paired samples *t*-test). Effect sizes on clinically relevant outcomes at postintervention and follow-up will be calculated by Cohen’s d using the means and pooled standard deviations of the measurements of the conditions. Effect sizes of .56-1.2 are considered large, .33-.55 are considered moderate, and less than .33 are considered small [54]. Repeated measures ANOVAs will be conducted to test for differences between the CBM Alcohol Avoidance Training and the CBM placebo condition on the secondary outcomes general health condition, depression, anxiety and stress. Mediation analyses will be conducted by applying the analytic procedure according to Preacher and Hayes [55] and Hayes [56] to examine whether a change in approach bias is mediating the Alcohol Avoidance Training effects on our primary outcome measure. Logistic regression analyses will be used to assess whether patient characteristics moderate the effect of the Alcohol Avoidance Training on our primary outcome measure. The procedure proposed by Baron and Kenny [57] will be adopted. Descriptive statistics will be used to investigate to what extent patients adhered to the Alcohol Avoidance Training (in terms of timing, frequency, and duration of sessions) and to what extent patients found the Alcohol Avoidance Training both acceptable and credible (testing adherence, acceptability, credibility).

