### Interventions

#### Treatment as Usual

TAU in this outpatient treatment setting is based on principles of CBT [33] and motivational interviewing [34]. The specific form of the TAU is tailored to the individual needs of the patient, in terms of treatment modality (Web-based or face-to-face) and intensity (brief 5-week version or intensive 3-month version). Study participants, therefore, receive an individualized version of treatment, as is common in regular real-world treatment settings. However, the basic ingredients for all versions are identical: daily registration, the analysis of the functions of the patients’ drinking behavior, behavioral change components, and motivational interviewing. Table 1 provides an overview of the main treatment ingredients. Sessions in face-to-face and Web-based treatment are identical. The only difference is that the contact with the therapist is synchronous in face-to-face treatment, and asynchronous via the Internet in the Web-based treatment [35]. The intensive version of the treatment takes approximately three months with (online or face-to-face) sessions once or twice a week and daily self-reporting of alcohol intake during the whole program. This treatment consists of two parts: a first part focusing on the analysis of the patients’ drinking habits, and a second part starting with the goal setting assignment, followed by sessions geared towards helping the patient reach the set goals and desired behavioral change. The brief 5-week version of the treatment focuses solely on behavioral change (part 2) and is intended for patients who already gained insight into their drinking habits when starting with treatment.

As we are interested in the effectiveness of online CBM Alcohol Avoidance Training as an adjunct to TAU, we do not differentiate between these four treatment “subgroups.” Due to the randomization, the experimental and control group are expected to be balanced concerning treatment modality and intensity.

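### Baseline significance tests are read as proof of randomisation, adjustment is left open, and the minimisation factor is not named in the primary model

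*Protocol article*

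**What the plan says.** All statements are in the protocol article.

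- **Statistical Analyses, baseline tests.** One-way ANOVAs and chi-square tests "will be performed to see if there are any significant differences at baseline between the two CBM training conditions", "for any of the demographic variables or outcome measures". The reading given to them is "Nonsignificant differences will indicate successful randomization".
- **Statistical Analyses, primary model.** "a logistic regression analysis will be used to test the differences in the proportion of patients reaching the low-risk drinking criterion" between the active and placebo training, at posttest and follow-up. No covariate is named. The next sentence begins "If necessary, baseline confounders will be controlled for", without saying what would make control necessary.
- **Randomization.** Allocation is computer-generated, 1:1, "using the method of minimization [51] in order to balance for type of TAU (online vs face-to-face"). Each patient goes to the arm that so far has fewest patients of that TAU type.
- **Treatment as Usual.** "we do not differentiate between these four treatment" subgroups (modality by intensity). The reason given is that randomisation should balance them.

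**The concern.** There are three linked weaknesses.

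1. The allocation is made by computer without the investigators. Unless that process fails, any baseline difference is due to chance, and the null hypothesis of each baseline test is true by design. A non-significant result therefore does not certify the randomisation, and a significant one does not discredit it.
2. The need for adjustment has no stated criterion. If the baseline tests supply it, covariates enter because of chance imbalance and not because they predict drinking. If they do not, there is no criterion at all. Either way the primary model is settled only after baseline data are seen.
3. Balancing on TAU type reduces the true variance of the treatment comparison when TAU type predicts success. A model without that factor does not credit the reduction, so its standard error is too large.

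At stake are the clarity of the primary analysis and some power. The validity of the type I error rate is not at stake.

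**Working it through.** **The plan's own figure.** Inputs from Sample Size Calculation: 68% v 81%, one-sided alpha 0.05, power 0.80, Fisher's exact test. Full enumeration gives power 0.7999 at 151 per arm and 0.8030 at 152. The stated 152 per arm reproduces, and this point does not change it. It also leaves little power to spare.

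**Chance of a baseline flag.** The article does not give the number of tests, so it is assumed.

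- The measures listed suggest about 10: four demographics (gender, age, education, employment) plus weekly consumption, approach bias, health status, depression, anxiety and stress.
- Five case-history items (duration of dependence, detoxifications, treatments, abstinence, medication) make 15. Craving, self-efficacy and motives move it towards 20.
- For k independent tests at 5%, P(at least one flag) = 1 − 0.95^k.
- Results: k = 5, 23%; k = 10, 40%; k = 15, 54%; k = 20, 64%.

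**What choosing covariates by test achieves.** Simulation of 304 patients randomised 1:1, with ten independent baseline covariates of which one is prognostic. Treatment log odds ratio = logit(0.81) − logit(0.68) = 0.696. One-sided 5% test.

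| Strength of the prognostic covariate (log-odds per SD) | Power, unadjusted | Power, covariates chosen by p<0.05 | Power, prognostic covariate pre-specified |
|---|---|---|---|
| 0.5 | 0.7965 | 0.7945 | 0.8175 |
| 1.0 | 0.7375 | 0.7395 | 0.7915 |

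With no treatment effect, the rejection rate stayed between 0.046 and 0.053 for all three approaches. Choosing by test gains essentially nothing; naming the covariate in advance gains about 2 to 5 points.

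**Leaving out the minimisation factor: variance.** With TAU type balanced across arms and equal numbers of each type, the arm-only variance is overstated by the ratio m(1−m) / mean[p(1−p)], where p is the success rate in each TAU type and m their mean. The only rate in the documents is 68% for Web-based treatment, so the gaps are assumptions.

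- 68% v 50%: 0.2419 / 0.2338 = 1.035
- 75% v 40%: 0.2444 / 0.2138 = 1.143
- 88% v 48%: 0.2176 / 0.1776 = 1.225, or √1.225 = 1.107 in standard error

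**Leaving out the minimisation factor: power.** Simulation of the stated minimisation rule (ties broken at random): 304 patients, TAU types about 50:50, control success averaging 68%, log odds ratio 0.696. Both models are fitted to the same simulated trials.

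| Gap between TAU types | Power without TAU type | Power with TAU type |
|---|---|---|
| 0 points | 83.8% | 83.8% |
| 10 points | 82.9% | 83.3% |
| 20 points | 80.1% | 81.1% |
| 30 points | 78.8% | 80.9% |
| 40 points | 74.5% | 79.4% |

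At a 40-point gap with no treatment effect, the arm-only standard error averages 0.247 against an actual spread of 0.225. The ratio is 0.247 / 0.225 = 1.10, in line with the 1.107 above. The one-sided error rate falls to 0.037. With TAU type in the model it lies between 0.044 and 0.052 at every gap.

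Simulation error is about 0.3 points for error rates and up to about 1 point for each power figure.

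**The case against.** The case on the other side has real force on several points.

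- **The link from tests to adjustment is inferred.** A reader might infer that the protocol selects covariates by p-value. It does not say so. The sentence on the primary model stands between the tests and the adjustment clause, and the word confounder ordinarily implies some relation to outcome. This stands. What can be said is that no other criterion is given.
- **TAU type is unnamed, not excluded.** A reader might infer an arm-only model. The article gives no covariate list either way, and the Treatment as Usual remark concerns four modality-by-intensity groups, not the two-level factor. A condensed article may leave the list to an analysis plan. This also stands. However, the article does state that it relies on balance, and it fixes an open-ended adjustment clause.
- **The harm is small and on the safe side.** The face-to-face success rate is not given, and the article says sessions are identical in both modalities, so a 40-point gap has no support in the text. Up to about 20 points the loss is roughly one point of power. This stands.
- **The count of baseline tests is assumed and the measures are probably correlated.** This stands for the exact percentages. It does not rescue the claim that non-significance shows successful randomisation, which is wrong at any count and which no analysis plan could make right.
- **Adjustment is not entirely free.** In a logistic model, prognostic covariates change the odds ratio from marginal to conditional. In the simulation with a 40-point gap, the mean log odds ratio was 0.60 unadjusted and 0.71 adjusted. This stands and is dealt with in the fix.

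**Conclusion.** The point holds in a limited form. The sentence on successful randomisation is wrong in itself. The adjustment clause leaves the primary model open until baseline data are seen; that the baseline tests would decide it is the natural reading, but an inference. The only minimisation factor is not named in the stated primary model.

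The cost is efficiency: about 1 point of power at an assumed 20-point gap between TAU types and about 5 at 40, given equal numbers of each type. A pre-specified prognostic covariate could add some 2 to 5 points under the assumed strengths.

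A reader might go further and conclude that the primary result would be invalid or the false-positive rate inflated. The calculations do not support that: the error rate stays near 5% when covariates are chosen by test, and falls below 5% when a strongly prognostic TAU type is omitted.

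**What to change.** In Statistical Analyses:

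1. Delete the sentence on successful randomisation, drop the baseline tests as a criterion for anything, and present baseline values by arm descriptively.
2. Replace the conditional adjustment clause with a fixed statement: the primary logistic regression includes TAU type (online or face-to-face) and baseline weekly alcohol consumption, and no covariate is chosen by test. Table 2 shows consumption both at TAU baseline and at preassessment, so say which is used.
3. State that the adjusted odds ratio is conditional on these covariates, or report a standardised risk difference beside it.

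Sex and TAU intensity are optional additions; the documents give no evidence that they are prognostic.

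The cost is a few sentences and the small added burden of explaining a conditional odds ratio. TAU type and consumption are already recorded, and the sample size of 152 per arm is unchanged.

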### Aims and Hypotheses

The aim of the current study is to investigate the effectiveness of online CBM Alcohol Avoidance Training as an adjunct to TAU in an outpatient treatment setting. Patients receive eight sessions of either the active or placebo version of the CBM Alcohol Avoidance Training during their TAU. The primary goal is to test the effects of this adjunct CBM on alcohol use immediately after finishing the intervention and three and six months later, by looking at the changes in the level of alcohol consumption over a week. The primary outcome measure is the percentage of the patients reaching the low-risk drinking level, defined as <22 standard units/week for men and <15 for women [29]. It is expected that more patients in the experimental condition will reach low-risk drinking level. Furthermore, it is hypothesized that the CBM intervention decreases or reverses the approach bias, and these changes are expected to mediate the effects on alcohol use [23]. An improvement in health status and a decrease in depression, anxiety and stress for patients in the training condition, compared to the placebo condition, are expected as secondary outcomes. To investigate who benefits most from the training, possible moderators will be examined. Automatic impulses may be controlled by cognitive capacity available to inhibit these impulses. Refusal self-efficacy is considered such a cognitive resource. Following this assumption, CBM interventions can yield benefits, especially for those with a relatively weak cognitive control over their impulses to drink [12,30-32]. In line with the predictions from dual process models and prior CBM trials [12], it is expected that for patients with a low baseline self-efficacy, the additional effect of the Alcohol Avoidance Training will be stronger. Similarly, time-varying self-efficacy is expected to partially mediate the CBM effect as repeated experiences of successful coping due to stronger avoidance responses will enhance refusal self-efficacy. Patients’ adherence and perceptions of treatment acceptability, and credibility will also be examined.

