### Primary and Secondary Outcome Measures

The primary outcome measure for this study will be *the proportion of patients reporting alcohol consumption below low-risk drinking limits* (<22 standard units/week for men and <15 for women) [29], since achieving safe drinking is the primary aim of alcohol addiction care. This will be assessed using the TLFB method [40]. As it was not feasible to verify whether all participants met this threshold at the start of treatment and with the knowledge that a previous trial with a similar target group showed that enrolled participants only very rarely report below-threshold consumption levels at baseline [35]-, we allowed all patients to enroll in the study. If necessary, corrections will be made in the analyses.

Secondary outcome measures include changes in approach bias measured by an AAT in the preassessment and postassessment. An AAT bias index is calculated as the difference between the median reaction time scores for pushing pictures of one category (alcoholic beverages or soft drinks) and the median reaction time score for pulling pictures of that category. Median scores are used to minimize the influence of outliers. Positive scores indicate approach tendencies whereas negative scores indicate avoidance tendencies. Furthermore, it is investigated whether the added effect on treatment outcome is mediated by the amount of change in approach bias and who benefits most from training by identifying patient characteristics that moderate the outcome of the training. Other secondary outcome measures are general health condition, depression, anxiety and stress, intervention credibility and patient satisfaction.

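### The primary outcome is tested at several visits and none is ranked as primary, although the sample size is for one test; if any one visit suffices, the chance of a false claim of benefit is about 10–13% over three one-sided tests, not 5%

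*Protocol article*

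**What the plan says.** All places are in the Protocol article.

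- **Aims and Hypotheses.** The primary goal is the effect on "alcohol use immediately after finishing the intervention and three and six months later", which is three time points.
- **Primary and Secondary Outcome Measures.** The primary outcome is "the proportion of patients reporting alcohol consumption below low-risk drinking limits". The definition carries no time point.
- **Statistical Analyses.** One logistic regression approach is to determine the primary outcome, comparing the "CBM Alcohol Avoidance Training and CBM placebo condition, both at posttest and at follow-up". The section gives no order among the visits and does not say whether one or all must be significant. It states no alpha or sidedness for these regressions.
- **Sample Size Calculation.** The control rate is 68% and the expected rate is "81% achieving the safe drinking criterion (beta>.80; alpha (one-tailed) <.05". The result is that "152 patients are needed within a condition to show the hypothesized effects". This is one comparison of two proportions.
- **Table 2.** Weekly alcohol consumption is ticked at both the postassessment (end of CBM training) and *Posttest TAU*. There is a single *Follow-up* column.
- **Timing of follow-up.** Trial Design counts three and six months from the end of TAU. Participants and Procedure counts them from the postassessment.

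**The concern.** The visit is part of what defines a primary outcome. Here the text determines the primary outcome by tests at more than one visit without saying which one answers the trial's question. If the visits disagree, for example a benefit at the end of training that has gone by six months, the protocol does not say whether the trial has succeeded. If any significant visit may be claimed, the 5% used to size the trial is not the error rate of the overall claim.

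Two wording problems add to this. *Posttest* could mean the CBM postassessment or the end-of-TAU visit, and these can fall at different times because TAU lasts about five weeks or about three months. The follow-up visits also have two starting points.

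**Working it through.** **Inputs from the Protocol article.** Control rate 68% ("It has been shown that the Web-based treatment resulted in a 68% success rate"); expected rate 81% (+13 points); one-tailed alpha .05; power .80; Fisher's exact test; 1:1 allocation ("with an equal likelihood, using the method of minimization"); 152 per arm.

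**Assumed.** The correlation between the test statistics at different visits is not given. I take 0.3 to 0.7 as the working range and show 0 and 0.9 as well.

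**Step 1. Reproduce the stated sample size.** Exact unconditional power of the one-sided Fisher test at 5%, 68% v 81%:

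- n = 151 per arm: 0.7999
- n = 152 per arm: 0.803

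So 152 is reproduced, for exactly one one-sided test at 5%. A two-sided 5% Fisher test with 152 per arm would have power 0.70. The design contains no allowance for several primary tests.

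**Step 2. Chance of at least one false positive for benefit, each test one-sided at 5%, if any one visit suffices.**

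Independent tests: 1 − (1 − 0.05)^k.

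- k = 2: 1 − 0.95² = 9.75%
- k = 3: 1 − 0.95³ = 14.3%
- k = 4: 1 − 0.95⁴ = 18.5%

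Whatever the correlation, the upper bound is k × 5%, which is 15% for three tests.

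Equicorrelated normal test statistics with correlation ρ: 1 − ∫ φ(t) · Φ((1.645 − √ρ·t)/√(1 − ρ))^k dt.

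| Tests | ρ = 0 | 0.3 | 0.5 | 0.7 | 0.9 |
|---|---|---|---|---|---|
| 2 (posttest, one follow-up) | 9.75% | 9.3% | 8.8% | 8.0% | 6.8% |
| 3 (end of intervention, 3 and 6 months) | 14.3% | 13.0% | 11.8% | 10.3% | 8.0% |
| 4 (adding Posttest TAU) | 18.5% | 16.4% | 14.4% | 12.0% | 8.8% |

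**Step 3. The same if the regressions are two-sided at 5%.** Each test then has a 2.5% chance of a false result in favour of the training. Three tests give 1 − 0.975³ = 7.3% if independent, 6.3% at ρ = 0.5 and 5.5% at ρ = 0.7, against 2.5% for one test.

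**Step 4. What each remedy does to the sample size.**

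- One named primary visit: 152 per arm and 80% power stand as calculated.
- Bonferroni over three visits (one-sided 0.05/3 = 0.0167): power per test with 152 per arm falls to 64%, and 211 per arm are needed for 80%.

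**The case against.** **The inflation rests on a rule that the text does not state.** Nowhere does the article say that one significant visit is enough. If benefit were required at every visit, the error would be at most 5%. This stands: the figures are what follows under one reading that the text leaves open, not what it prescribes.

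**One-tailed testing is stated only for the sample size.** This also stands, which is why Step 3 gives the two-sided figures. They are about half as large, but still two to three times the 2.5% for a single test.

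**The number of tests is open.** Table 2 has one *Follow-up* column, so two tests is a possible reading. The aims make three the more natural one. A reader might go further, count *Posttest TAU* as a fourth primary test and put the error at up to 16%. The documents do not support that as the main figure. The aims tie the first time to the end of the intervention, and the postassessment directly follows the last training session. Table 2 shows only that consumption is collected at the end of TAU, as it also is at baseline and during training. With three tests at 5%, 16% is impossible, since the bound is 15%.

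**Multiplicity procedures are commonly left to an analysis plan.** That is fair, and the absence of an adjustment procedure is not counted here as a fault in its own right. What remains is a positive statement in the article: the primary outcome is determined at more than one visit, none ranked, beside a sample size for one test. A later adjustment such as Bonferroni would not be neutral, because it would undo the stated power.

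**The sample size does not point clearly to one visit.** The +13 points comes from long-term abstinence, but the article gives no time point for the 68% control rate. This stands, and it limits how firmly any particular visit can be recommended.

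**Conclusion.** The point holds. The article spreads the primary outcome over several visits and ranks none, while 152 per arm is reproduced for exactly one one-sided 5% test.

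On the most natural reading (three one-sided 5% tests, any one sufficient), the chance of a false claim of benefit is about 10–13% for assumed correlations of 0.7 to 0.3, with 14.3% under independence and about 8% at 0.9. The range moves with the reading: about 8–10% for two tests, about 12–16% if the end-of-TAU visit were also a primary test, and about 5.5–7.3% against 2.5% for three two-sided tests. All these figures assume that success at any one visit suffices; a requirement of success at all visits would remove the inflation.

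The need to name a primary visit does not depend on which figure applies, because under none of these readings does the text say which result answers the primary question.

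**What to change.** 1. Name one primary time point for the proportion of low-risk drinkers, using its Table 2 label, and tie the sample size statement to it. The six-month follow-up is a reasonable candidate because the assumed +13 points comes from long-term abstinence, but the choice is the sponsor's.
2. Declare the other visits secondary, or test them after the primary one in a fixed sequence at the same alpha.
3. State whether *posttest* means the CBM postassessment or *Posttest TAU*.
4. Reconcile the two starting points for follow-up in Trial Design and in Participants and Procedure, since they can place the same follow-up visit at different times.
5. State the alpha and sidedness of the primary regression, so that it matches the sample size calculation.

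**Cost.** A few sentences, to be settled before any unblinded analysis. No extra patients or data are needed, and 152 per arm and the stated alpha stand. The downside is that the other visits lose primary status. If the sponsor prefers to keep several primary visits with Bonferroni, the sample size must be recalculated (about 211 per arm for three).
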